## Abstract

**Introduction:**

Namibia is a high tuberculosis (TB)-burden country with an estimated incidence of 460/100 000 (around 12 000 cases) per year. Approximately 4.5% of new cases and 7.9% of previously treated TB cases are multidrug resistant (MDR) and 47% of patients with MDR-TB are HIV coinfected. Published data suggest a clustering of MDR-TB transmission in specific areas. Identifying transmission clusters is key to implementing high-yield and cost-effective interventions. This includes knowing the yield of finding TB cases in high-transmission zones (eg, community hotspots, hospitals or households) to deliver community-based interventions. We aim to identify such transmission zones for enhanced case finding and evaluate the effectiveness of this approach.

**Methods and analysis:**

H3TB is an observational cross-sectional study evaluating MDR-TB active case finding strategies. Sputum samples from MDR-TB cases in three regions of Namibia will be evaluated by whole genome sequencing (WGS) in addition to routine sputum investigations (Xpert MTB/RIF, culture and drug susceptibility testing). We will collect information on household contacts, use of community spaces and geographical map intersections between participants, synthesising these data to identify transmission hotspots. We will look at the feasibility, acceptability, yield and cost of case finding strategies in these hotspots, and in households of patients with MDR-TB and visitors of hospitalised patients with MDR-TB. A compartmental transmission dynamic model will be constructed to evaluate the impact and cost-effectiveness of the strategies if scaled.

**Ethics and dissemination:**

Ethics approval was obtained. Participants will give informed consent. H3TB will capitalise on a partnership with the Ministry of Health and Social Services to follow up individuals diagnosed with MDR-TB and integrate WGS data with innovative contact network mapping, to allow enhanced case finding. Study data will contribute towards a systems approach to TB control. Equally important, it will serve as a role model for similar studies in other high-incidence settings.

STRENGTHS AND LIMITATIONS OF THIS STUDYState-of-the-art sequencing techniques are implemented and used in a low-income and middle-income country setting at the University of Namibia (UNAM).Novel drug-resistant tuberculosis (DR-TB) case finding strategies are piloted and evaluated for feasibility, acceptability, yield and cost.The study is implemented in three Namibian regions which would make the findings generalisable; the transmission model will inform on the impact of scale-up of the case finding strategies in the whole country.Existing partnerships between the research group, the National TB and Leprosy Programme (NTLP), the Research Center Borstel and the Ministry of Health and Social Services, could be leveraged to support implementation.The study team depends on an existing partnership between UNAM and the NTLP/National Institutes of Pathology to obtain sputum culture samples for sequencing; if the routine collection and evaluation of sputum samples do not happen systematically, DR-TB cases might be missed.

## Introduction

Namibia is classified by the WHO as a high tuberculosis (TB)-burden country and, in 2020, the TB incidence was estimated to be 460/100 000, with 12 000 new cases/year.^1^ The most recent nationwide anti-TB drug resistance survey in Namibia was completed in 2015, reporting a prevalence of multidrug-resistant (MDR)-TB at 4.5% among new cases and 7.9% among previously treated cases. Approximately 46.6% of patients with MDR-TB were coinfected with HIV.^2^ Based on that prevalence, the number of MDR-TB cases/year is estimated to be around 800. Only 213 cases were detected in 2020.

Namibia faces significant challenges at every step along the TB care cascade, from preventive therapy to diagnostics and patient treatment. Challenges also exist in the identification of prevalent cases of TB infection and disease through passive and active case finding intervention strategies.^3^ During the COVID-19 pandemic, Namibia observed an increased number of missed or undiagnosed TB cases with case management interruptions due to the diagnostic supply chain, redirections of resources and the effects of human movement restrictions, negatively impacting care-seeking.^4^

In the ‘hotspots, hospitals, and households’ (H3TB) study, we aim to identify MDR-TB transmission clusters, through genomic, geospatial and social data interferences, which could indicate transmission hotspots. We aim to determine the diagnostic yield of targeting these areas for active case finding as well as evaluating the cost-effectiveness of such approaches. Our central hypothesis is that geographical heterogeneity in the concentration of genotypes exists within the MDR-TB epidemic in Namibia leading to high-transmission areas (hotspots), where MDR-TB incidence could be up to three times that of the baseline population. Further, if these areas could be identified and targeted through enhanced case finding strategies, these strategies might be more effective than screening and treatment programmes which do not adapt to spatial and biological variation.^5^ In addition to targeting transmission hotspots, our focus will be on MDR-TB screening of household contacts of MDR-TB cases and visitors of hospitalised patients with MDR-TB.

## Methods and analysis

### Patient and public involvement

We have collaborated directly with the National TB and Leprosy Programme (NTLP) ([name], coauthor) on the development of this protocol and with the national reference laboratory, the National Institutes of Pathology (NIP) ([name]). Since we are a young research group, we have not yet instituted community advisory boards (CABs) to discuss potential studies with community members. However, in a subsequent study, we have funding and the expertise to establish a CAB. The University of Namibia (UNAM) research ethics committees will incorporate community members from 2024 onwards.

### Design

This is an observational study including the design and evaluation of case finding intervention strategies to determine feasibility. The study has three objectives (table 1). In figure 1, the study flow is illustrated. Among an ongoing parent surveillance study which includes all MDR-TB cases in Namibia from all regions, H3TB is nested within three regions (Khomas, Otjozondjupa and Ohangwena). These regions are known to have a high TB incidence. In areas in the Otjozondjupa region, the case notification rate has been >1000/100 000 (submitted for publication, [name]). The ongoing parent surveillance study informs the H3TB research team on potential participants to include in objective 1. In addition, a scoping review looks at existing MDR-TB case finding strategies in low-income and middle-income countries (LMICs) and informs objective 2. Data from the surveillance study and the first two objectives inform the development of the dynamic transmission model, which is objective 3.

**Table 1 T1:** Objectives of H3TB Study

Objective	Activity
1	To identify transmission hotspots using routine data from the National TB and Leprosy Programme, whole genome sequencing, geospatial and social data from the research study
2	To conduct a feasibility study of three active case finding interventions in three geographical regions
3	To develop a dynamic transmission model to determine the impact of scaled-up interventions on MDR-TB incidence and evaluate cost-effectiveness

H3TB, hotspots, hospitals, and households; MDR-TB, multidrug-resistant TB; TB, tuberculosis.

**Figure 1 F1:**
[figure not shown]
Flow diagram of H3TB Study design. Black text indicates methods; orange text indicates outcomes. DST, drug sensitivity testing; H3TB, hotspots, hospitals, and households; MDR-TB, multidrug-resistant TB; p.a., per annum; TB, tuberculosis.

### Setting

The study will be conducted in Namibia in three regions, viz., Khomas, Ohangwena and Otjozondjupa. Recruitment has commenced in August 2022 and will continue until December 2024.

### Objective 1

#### Participant identification

Individuals with a positive Xpert MTB/RIF result with rifampicin resistance demonstrated, and a positive *Mycobacterium tuberculosis* culture, will be included from the three regions. To identify transmission hotspots, whole genome sequencing (WGS) results will be combined with clinical, epidemiological, geospatial and social network data. A traditional sample size calculation is not indicated if most of the MDR-TB cases in a region are included (>80%).^5 6^ In this study, we might miss some MDR-TB cases who are not reported or diagnosed. However, a current surveillance study which started in January 2020 and is ongoing could inform on additional participants from these areas. We will look at other strategies, like including participants from other regions or finding additional cases through collaborating with the NTLP’s active case finding interventions, to ensure robustness of our data.

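### Objective 1 rests its lack of a sample-size justification on including more than 80% of MDR-TB cases in a region, but the only detection figure given (national, 2020) is about 27%

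*Protocol article*

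**What the plan says.** Objective 1, Participant identification, gives one reason for having no sample-size calculation: "A traditional sample size calculation is not indicated if most of the MDR-TB cases in a region are included (>80"%). No target number, precision or expected coverage is put in its place. Eligibility is limited to "Individuals with a positive Xpert MTB/RIF result with rifampicin resistance demonstrated, and a positive" culture. The section concedes that some unreported or undiagnosed cases could be missed and names three remedies. One is the surveillance study running since January 2020. The other two are measures "like including participants from other regions or finding additional cases through collaborating with the" national programme's active case finding.

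The Introduction gives the burden: "the number of MDR-TB cases/year is estimated to be around 800. Only 213 cases were detected in 2020". It also gives the inputs behind that estimate: "the TB incidence was estimated to be 460/100 000, with 12 000 new cases/year", and "MDR)-TB at 4.5% among new cases and 7.9% among previously treated cases".

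**The concern.** The waiver is conditional on near-complete inclusion. The article never says whether the condition is expected to hold, and its own burden figures point well away from it. To concede that some cases may be missed does not describe a setting where, on the only figures given, about three in four were not detected.

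Coverage matters because Objective 1 (Laboratory analyses) takes two or more isolates within five SNPs as the proxy for direct transmission. A case whose linked cases were never sampled looks unclustered. Under Objective 1, Data management and analysis, clusters help to define hotspots. The Discussion says hotspots will be used to select sites for the case-finding study, and Objective 3 draws on data from Objectives 1 and 2. A shortfall in sampling therefore affects more than the Objective 1 description.

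**Working it through.** **Inputs.** From the Introduction: 12 000 TB cases a year, MDR-TB 4.5% in new and 7.9% in previously treated cases, about 800 MDR-TB cases a year, and 213 detected in 2020. From Objective 1, Participant identification: the threshold of more than 80%.

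**1. The article's figure of 800.** Let s be the previously treated share, which is not given. The total is 12 000 × [(1 − s) × 0.045 + s × 0.079].
- s = 0: 12 000 × 0.045 = 540.
- s = 1: 12 000 × 0.079 = 948.
- 800 is matched at s = (800/12 000 − 0.045)/(0.079 − 0.045) = 0.64.

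Since s is not stated, 800 can be neither confirmed nor called wrong. If the 12 000 are all new cases and previously treated cases come on top, the total is at least 540, so 540 remains the most favourable denominator.

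**2. Detection.**
- 213/800 = 26.6%.
- 213/948 = 22.5%.
- 213/540 = 39.4%.

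**3. Distance from the condition.**
- 0.80 × 800 = 640 detections a year, which is 427 more than 213, and 640/213 = 3.0 times as many.
- With the most favourable total, 0.80 × 540 = 432, and 432/213 = 2.0 times.
- Conversely, 213 is 80% only of a total of 213/0.80 = 266.

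**4. From detection to enrolment.** Only diagnosed, Xpert rifampicin-resistant, culture-positive people can enter, so coverage cannot exceed detection. The article gives no retention figures. As an assumption, 80% retention at each of culture and consent gives 0.266 × 0.80 × 0.80 = 17%.

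**5. The remedies.**
- Surveillance study: it adds people who are already diagnosed. It may recover some who were not enrolled, but it does not lift the detection ceiling. Reaching back to 2020 adds to numerator and denominator alike.
- Other regions: these add participants, but not coverage within a region.
- Programme active case finding: this could raise detection. No size is given, and it adds cases only where searching takes place.

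**6. Effect on clustering.** If members of a true cluster of size k are sampled independently with probability f, a sampled case is seen as clustered with probability 1 − (1 − f)^(k−1).

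| Coverage f | k = 2 | k = 3 | k = 5 |
|---|---|---|---|
| 80% | 80% | 96% | 99.8% |
| 39.4% | 39% | 63% | 87% |
| 26.6% | 27% | 46% | 71% |
| 17% (assumed retention) | 17% | 31% | 53% |

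For example, at f = 0.266 and k = 3: 1 − 0.734² = 0.46.

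**The case against.** The strongest reply is that 27% is national and from 2020, while the condition applies within a region and recruitment runs from August 2022 to December 2024 (Setting). The Introduction says missed and undiagnosed cases increased during the pandemic, so 2020 may be unusually low. This stands: 27% is an indicator, not a measured coverage for the study regions. A reader might infer that most cases in the three regions will be missed, but the document does not establish that. It is still the only figure offered. On the 2020 numbers, the three regions could have reached 80% only if they held at most 266/800 = 33% of national cases and nothing was detected elsewhere (266/540 = 49% on the smallest total). Nothing in the article suggests this.

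A second reply is that the waiver is worded as a condition and that missed cases are acknowledged, both here and in the strengths and limitations. The article does not claim to have reached 80%. That is fair, but the condition is the only justification given and nothing shows that it is met.

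Third, the clustering table assumes independent sampling. Linked cases found together, for instance through contact tracing, would make the table too pessimistic. Hotspots are also defined from TB incidence, social network and spatial data as well as sequencing, so a missed genomic pair need not lose a hotspot. The Objective 3 model is calibrated to external Namibian data too. These points limit the consequence without removing it.

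A reader might also infer that the remedies cannot raise coverage at all. That goes too far, because active case finding could. Nor do the documents require the main hotspot map to rest on passively detected cases alone. That would lower coverage further and keep any bias towards places with good access to diagnosis.

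**Conclusion.** The point holds in a limited form. The more-than-80% condition is not supported by the article's only detection figure, which is about 27% nationally in 2020 and 22% to 39% over the totals its stated rates allow. The remedies are not shown to reach 80%: two of the three do not lift detection within a region, and the third is unquantified and would need roughly a threefold gain against 800.

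The size of the effect on clustering depends on independent sampling and on regional coverage resembling the national figure. On those assumptions, a sampled case from a true pair is seen as clustered 27% of the time rather than 80%, with a smaller loss for larger clusters. What is wrong is the justification, and with it what an absent cluster can be taken to mean. The study is not invalidated.

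**What to change.** - Remove the more-than-80% condition as the justification for Objective 1.
- State expected coverage for each of the three regions with a range, citing about 27% nationally in 2020 as the available indicator. Replace the concession about some missed cases with that figure.
- Add a sensitivity analysis of clustering and hotspot identification over plausible sampling fractions, for example 15% to 40%, by simulation or down-sampling.
- Record each case's detection route, and show the hotspot map with and without cases found by active case finding.
- State that the absence of an observed cluster is not evidence that there is no hotspot.
- Do not count participants from other regions towards within-region coverage. They may still be included for other purposes, such as links across regions.

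The cost is a less favourable stated coverage, one data field and a modest amount of extra analysis. No additional recruitment is needed.

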#### Data management and analysis

Data will be captured into databases developed by a data specialist. WGS data will be analysed using a phylogenetic strain classification and a cluster/similarity analysis. Social network data will be analysed using thematic analysis for the description of typical and atypical social network contacts for people with MDR-TB in Namibia. Similarly, thematic analysis will be used for shared space data to identify the types of places where people with MDR-TB interact with other people to whom TB may be transmitted. Social network analysis, in conjunction with WGS cluster data, will indicate transmission hotspots within the regions. In our context, a hotspot is an area with a high TB incidence and where TB transmission happens, based on microbial genomic methods such as WGS and a collection of epidemiological approaches (social network and spatial analysis) and geographical map intersections between participants.

### Objective 2

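### Adding actively found cases to the Objective 1 data may make heavily searched places look like hotspots, because counts and genomic links both rise with local search effort

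*Protocol article*

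**What the plan says.** All references are to the protocol article.

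- **Inclusion (Objective 1, Participant identification).** The rule admits "Individuals with a positive Xpert MTB/RIF result with rifampicin resistance demonstrated" who are also culture positive and come from the three regions. It does not mention how the case came to be diagnosed.
- **Remedy for missed cases (same section).** The article accepts that some cases will be missed, notes that the surveillance study could supply more participants, and adds that further options will be considered, such as enrolling from elsewhere in the country or "finding additional cases through collaborating with the NTLP’s active case finding interventions". The stated purpose is robustness of the data. The same section drops a sample size calculation on the ground that one is not needed when more than 80% of a region's MDR-TB cases are included.
- **Hotspot definition (Objective 1, Data management and analysis).** "a hotspot is an area with a high TB incidence and where TB transmission happens", judged from sequencing, social network and spatial evidence. The Laboratory analyses section takes a distance of at most five SNPs between isolates as the proxy for direct transmission.
- **Burden and hypothesis (Introduction).** MDR-TB cases are put at about 800 a year; "Only 213 cases were detected in 2020". The central hypothesis is that there are hotspots "where MDR-TB incidence could be up to three times that of the baseline population".
- **Timing (Setting, Discussion).** "Recruitment has commenced in August 2022 and will continue until December 2024"; this is one window for the whole study. The Discussion says that the hotspots, once identified, will be used to select feasibility sites.

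**The concern.** Active case finding is carried out in chosen places. Where it runs, more of the existing cases are diagnosed; where it does not, the count stays at the routine level. A map that pools both kinds of case partly shows where people searched. Genomic evidence does not cancel this, because a link within five SNPs can be seen only if both isolates were collected. Each added case also brings an interview and GPS points, so the social and spatial evidence grows with the same effort.

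The first part of the central hypothesis, the choice of hotspot screening sites in Objective 2 and the inputs to the Objective 3 model all rest on this case set. A step offered as a safeguard could therefore bias the result it is meant to protect.

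A second, weaker route exists. Objective 2 participants who test rifampicin resistant have culture done, so a culture-positive person found by household or ward-visitor screening in the three regions could also meet the Objective 1 rule. Such people are tied to a known case from the start. The article gives no cut-off between the objectives. This route is an inference; the article does not state it.

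**Working it through.** **Inputs from the article (Introduction; Objective 1, Participant identification):** 12 000 TB cases a year; MDR share 4.5% (new) and 7.9% (previously treated); about 800 MDR-TB cases a year; 213 detected in 2020; hypothesised excess of as much as threefold; 80% coverage threshold.

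**Assumptions, not in the article:** the fraction *f* of missed cases that active search finds, the detection share *p1* in a searched area, and the transmission chain size *m*. Local detection shares are not given, so the national share stands in for an unsearched area.

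**Step 1. The figure of 800.** Cases = 12 000 × [4.5%(1 − s) + 7.9%s], where *s* is the share previously treated.
- All new: 12 000 × 0.045 = 540.
- All previously treated: 12 000 × 0.079 = 948.
- The value 800 needs s = (800/12 000 − 0.045)/(0.079 − 0.045) = 64%.

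The article does not give *s*, so 800 can be neither confirmed nor refuted. The range 540 to 948 is carried forward.

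**Step 2. National detection share.** p0 = 213/800 = 26.6%; 213/540 = 39.4%; 213/948 = 22.5%.

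**Step 3. Apparent case ratio, searched to unsearched area, equal true incidence.**

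For a fraction *f* of missed cases found, ratio = [p0 + f(1 − p0)]/p0. For detection raised to *p1*, ratio = p1/p0.

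| Scenario | True total 540 | True total 800 | True total 948 |
|---|---|---|---|
| Half of missed cases found | 1.8 | 2.4 | 2.7 |
| Detection raised to 80% | 2.0 | 3.0 | 3.6 |
| All cases found | 2.5 | 3.8 | 4.5 |

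Worked for 800: (0.266 + 0.5 × 0.734)/0.266 = 2.4, and 0.80/0.266 = 3.0. On the 800 figure, 80% detection means finding (0.80 − 0.266)/0.734 = 73% of the missed cases.

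**Step 4. Does the sequencing criterion remove the effect?** Take a chain of *m* cases in one area, all within the SNP threshold and each detected independently. The ratio of clustered cases per true case is

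p1[1 − (1 − p1)^(m−1)] / {p0[1 − (1 − p0)^(m−1)]}, with p0 = 26.6%.

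| p1 | m = 2 | m = 3 | m = 5 |
|---|---|---|---|
| 50% | 3.5 | 3.1 | 2.5 |
| 80% | 9.0 | 6.3 | 4.2 |

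For m = 2 at 80%: 0.80²/0.266² = 9.0. In each of these cells the inflation exceeds that of the plain case ratio (1.9 at 50%, 3.0 at 80%), so linkage is more sensitive to ascertainment than counts are.

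**Step 5. Even search.** If detection is the same everywhere, p1 = p0 and every ratio is 1.0. The artefact needs search effort that differs by place.

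**The case against.** **The remedy is conditional.** The team will look at several options, among them other regions and the surveillance study. A reader might infer a firm plan to add actively found cases and a certain distortion. The text supports neither: the addition is only being considered, and evenly spread active case finding would improve coverage without creating false contrasts. This stands, and the point is worded accordingly.

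**The Objective 2 feedback is not stated.** A reader might infer that screening in hotspots will feed the map that defined them. The Discussion puts hotspot identification before site selection, Table 1 refers to routine programme data, and the Objective 2 laboratory section mentions culture and drug sensitivity testing but no sequencing. Numbers in the hotspot arm would also be small. The Introduction implies a population of 12 000/(460/100 000) ≈ 2.6 million, hence about 31 MDR-TB cases per 100 000. At three times that, and taking prevalence as equal to annual incidence, 600 people screened yield about 0.55 cases. Cases from hotspot screening therefore matter little, and only if the map is updated. Household and ward-visitor screening does not depend on prior hotspot identification, so that part of the inference remains possible.

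**The 213 need not be passive detections.** The Introduction says only that they were detected. The figure is national and from 2020, when the pandemic disrupted diagnosis. This stands: 27% is a stand-in and the ratios are illustrations.

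**A hotspot is more than a case count.** The definition refers to TB incidence, not MDR-TB counts, and also requires genomic, social and spatial evidence. A ratio of 2.4 does not by itself make a hotspot. This is true, but step 4 shows that the genomic evidence moves with search effort too.

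**Handling of detection route may be in the full protocol.** That is possible, and silence on it is not the complaint. The point rests on what the article does say: it presents active case finding as a source of robustness, under an inclusion rule open to any route.

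**Conclusion.** The concern holds in a limited form. The article will consider enlarging the hotspot data with cases from the programme's active case finding, and its inclusion rule is open to any route of detection. If the search is uneven, searched places may look like hotspots on both counts and genomic links. Under the illustrative assumptions the apparent excess is about 2.4-fold (1.8 to 2.7) when half of the missed cases are found and about 3.0-fold (2.0 to 3.6) at 80% detection. That is the size of the hypothesised contrast, so the artefact could not be told apart from the effect by magnitude. These figures rest on equal true incidence, the national 2020 detection share and assumed search yields, none of which the article gives for the three regions.

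Entry of household or ward-visitor screening cases into Objective 1 is a plausible inference and no more. The documents do not show that bias will occur, nor that hotspot-site screening feeds the first map.

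**What to change.** In Objective 1, under Participant identification and under Data management and analysis:

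1. Record the route of detection for every case: routine diagnosis, programme active case finding, or H3TB screening.
2. Fix a data cut-off for the hotspot map, so that cases found by Objective 2 screening do not enter it.
3. Present the hotspot map and the cluster results with and without actively found cases, and call robust only those hotspots that persist without them.

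A primary map restricted to passively detected cases should not be required. Routine diagnosis also varies by place, and dropping cases would move the data further from the 80% coverage that the article invokes.

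The cost is one extra variable, one extra analysis and possibly fewer hotspots called robust. No added recruitment is needed.
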